### **7.7 METHODS OF COMPLIANCE**

#### **7.7.1 NUTRITIONAL COUNSELLING**

Nutritional counselling will be given at all main-group visits during and after the LCD diet.

#### **7.7.2 3-DAY DIET REGISTRATION**

On CID 1-4, adult subjects and overweight children will be instructed to register their daily diet in a food diary for 3 days. One of the days should be a day at the weekend. The subjects should not let the registration of food influence their daily diets. Instructions for the diet registrations will be the responsibility of a nutritionist.

#### **7.7.3 REGISTRATION OF THE DIET DURING THE INTERVENTION PERIODS**

During the dietary intervention period 1, all subjects (except those in the control group) will be supplied with all their food to take home from a purpose built shop at the Department of Human Nutrition.

Each food item will possess a bar code, and food items received by the subject will be registered in a database in the shop. This will allow accurate registration of the dietary intake with regard to total energy, energy from protein, fat and carbohydrates, simple sugars, fibre content, alcohol and energy density (calculated without drinks) etc.

Alcohol will not be available from the shop and the subjects are instructed to report their alcohol intake on a weekly basis (i.e. units (12g)/week). The subjects will be instructed to report any undamaged or uneaten food items in the shop within 14 days of purchase.

#### **7.7.4 BLOOD SAMPLES**

On CID 1-4, blood samples will be taken for analysis of specifically chosen markers that are expected or shown to differ in the dietary regimens (adults).

#### **7.7.5 24-H URINE SAMPLES**

24-h urinary collection (with PABA control) will be performed from every adult subject on CID 1, visit 11 and 14, CID 3 and 4 to assess urinary nitrogen and other relevant markers such as C-peptide. Subjects will be given written instruction on the 24h urinary sampling procedure.

### **7.8 ADVERSE EVENTS AND REGISTRATION OF ADVERSE EVENTS**

An AE is any unfavourable, unintended event (symptom, disease, or abnormal laboratory finding) reported by a subject or observed by the investigator during the trial, which does not necessarily have a causal relationship with the treatment. Any relevant AE and spontaneously reported symptoms must be recorded in the source data at every visit after the initial visit. Follow-up of any AE reported before the last day of the intervention should be performed according to medical indications. All AE will be recorded in the source data with information about the severity, frequency, date of onset, duration and action taken regarding participation in the study. In addition, the investigator must record the relationship between the AE and the intervention and the subject outcome.

The severity of the AE is recorded according to the following scale: Mild = Awareness of sign or symptom, but easily tolerated, Moderate = Discomfort sufficient to cause interference with normal activities and Severe = Incapacitating, with inability to perform normal activities.

A serious adverse event (SAE) is any untoward medical occurrence that:

- Results in death
- Is life-threatening
- Requires patient hospitalization or prolongation of existing hospitalization
- Results in persistent or significant disability or incapacity
- Is a congenital anomaly / birth defect

The subject must be admitted to hospital in order to be considered as receiving hospital treatment. Hospitalization itself and surgical diagnostic procedures are not AE. Hospitalization for elective surgery in a pre-existing condition that has not worsened during study participation is not an AE. A distinction should be drawn between serious and severe adverse events. A severe event is a major event of its type, but is not necessarily considered serious. For example, nausea, which persists for several hours, may be considered severe nausea, but not a SAE. On the other hand a stroke, which results in, only a limited degree of disability may be considered a mild stroke, but would be a SAE. Thus, a serious or non-serious event also refers to the nature of the event, in addition to the severity of an event.

In case of a SAE the responsible study investigator (i.e. [name], RVAU, Denmark, Coordinating Centre for RTD1) must be informed immediately by telephone and/or in writing, within 24 hours.

At least the following data are required for an immediate/expedited SAE report:

- Patient identification (initials, date of birth, patient number)
- Description of the SAE (symptoms, diagnosis). Every clinical finding in this context has to be reported completely.
- Seriousness of the SAE ("mild", "moderate", "severe") and reasons for the decision

- Causal relationship with the study participation ("probable", "possible", "not related", "not assessable")

In case of death during the study, a report of a post mortem examination has to be made. The investigator will notify the Ethics Committee according to the ICH-Guidelines "Note for Guidance on Clinical Safety Data Management: Definitions and Standards for Expedited Reporting" and "Note for Guidance on Good Clinical Practice" (ICH GCP).

### **7.8.1 REGISTRATION OF CONCOMITANT TREATMENT**

Relevant concomitant treatment must be registered in the source data. All concomitant treatments that are necessary for the subject's welfare and which do not fall outside the terms of the protocol may be continued during the trial. Increase in dosage as well as introduction of new medications during the trial must also be reported as an AE.

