### **5.3 PROCEDURE FOR EXCLUSION/DISCONTINUATION DURING THE STUDY**

A subject will be removed from the study treatment based on their own decision or if the investigator finds it medically necessary.

If any child or adult refuses to follow dietary instruction after starting the intervention, the other family members will still be allowed to continue in the study. However, if refusal (by adult or overweight child) occurs before the start of the LCD diet, then the family will not be included in the study.

When a subject decides to discontinue participation in the study, he/she should always be contacted in order to, if possible, obtain information about the reason(s) for discontinuation. Whenever possible, the subjects should return for an unscheduled visit at the time of or soon after discontinuation.

The following procedures should be performed at an unscheduled visit:

- Date of discontinuation
- Reason for discontinuation
- Adverse events
- Recording of any new concomitant drug therapy or any changes to ongoing concomitant drug therapy since last visit, any pharmacological treatment established prior to entrance in this study will be maintained as long as ethically possible
- DEXA scan or bioimpedance (body fat mass, body lean mass)
- Body weight
- Blood pressure
- Waist/hip and sagittal measurements
- Blood sample
- Compliance Questionnaire

Subjects may also be withdrawn from the study because of severe protocol violations.

These subjects will not be included in the analysis and will permanently be dismissed from the study. Reasons for dismissal should be carefully recorded in the source data.

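### Section 7.8.1 makes every new medication or dose increase an adverse event, which contradicts the adverse event definition in Section 7.8

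*Protocol*

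**What the plan says.** Section 7.8 of the protocol sets the definition: "An AE is any unfavourable, unintended event (symptom, disease, or abnormal laboratory finding) reported by a subject or observed by the investigator" during the trial, whether or not the intervention caused it. On recording it says: "Any relevant AE and spontaneously reported symptoms must be recorded in the source data at every visit after the initial visit". Each AE carries a grade ("The severity of the AE is recorded according to the following scale"), which runs from awareness of a symptom, through discomfort that interferes with activities, to incapacity. The section also separates an event from the medical response to it: "Hospitalization itself and surgical diagnostic procedures are not AE". Elective surgery for a pre-existing condition that has not worsened is likewise ruled out.

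Section 7.8.1 deals with concomitant treatment. It begins "Relevant concomitant treatment must be registered in the source data", allows necessary treatment to continue, and ends "Increase in dosage as well as introduction of new medications during the trial must also be reported as an AE". Nothing in that sentence restricts it by indication or cause.

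Elsewhere the protocol keeps the two kinds of record apart. The list for the unscheduled discontinuation visit in Section 5.3 names adverse events as one item and, as another, "Recording of any new concomitant drug therapy or any changes to ongoing concomitant drug therapy since last visit". The adult and child visit lists in Section 7.1 call for both adverse events and concomitant medication.

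**The concern.** The last sentence of Section 7.8.1 brings into the AE record something that the Section 7.8 definition keeps out. A prescription is a response to a condition, or a preventive or elective choice. It is not a symptom, disease or laboratory finding.

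What is at stake is the meaning of the AE record in a trial whose synopsis names safety alongside efficacy. Section 9.3 on the participation of children says that any AE observed in adults or children is reported to the Ethical Officer, with action decided by the Project Board. If the record mixes harms with drug starts, part of what reaches the Ethical Officer is prescribing activity. Staff would also have to give a severity grade to something that has none.

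**Working it through.** The protocol states no AE count or rate, so there is no figure to reproduce. The check sets the sections side by side and works through cases.

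**Step 1. Does a medication change meet the Section 7.8 definition?**

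| Element of Section 7.8 | New drug or dose increase |
|---|---|
| Unfavourable and unintended | Not necessarily; a prescription is intended |
| Symptom, disease or abnormal laboratory finding | None of the three |
| Gradable by awareness, discomfort or incapacity | No; only the condition treated can be graded |
| Medical response kept apart from the event | A drug is such a response, as hospitalization is |

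The Section 7.8.1 rule therefore conflicts with the definition, with the grading scale and with the way Section 7.8 treats hospitalization.

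**Step 2. What happens to single cases when both sections are followed literally?**

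| Case | AE records under 7.8 alone | AE records under 7.8 and 7.8.1 |
|---|---|---|
| Headache, no drug | 1 | 1 |
| Sore throat, antibiotic started | 1 | 2 |
| Oral contraceptive started, no complaint | 0 | 1 |

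The contraceptive is a fair example, because Section 5.1 exempts it from the bar on regular medication at entry. The second record for the sore throat needs both sections: 7.8 requires the condition to be recorded and 7.8.1 makes the drug an AE. Neither section links the two records or says that one replaces the other.

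**Step 3. Which summaries move?**

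- Event count: let f be the share of AE conditions that lead to one new drug or dose increase, and r the number of drug starts with no harm behind them per AE condition. Then 100 conditions give 100 × (1 + f + r) records.
- The protocol gives neither f nor r. As an assumption, with r = 0: f = 10% gives 100 × 1.10 = 110 records, f = 30% gives 130, and f = 50% gives 150. Any r above zero adds 100 × r more.
- Share of subjects with at least one AE: the sore throat subject counts once under either rule, so double records leave the share unchanged. It rises only where a subject's sole record is a start that is not a harm.
- Ratio of event counts between diets: if f and r are the same in every arm, the factor (1 + f + r) cancels. The protocol gives no reason to expect them to differ. The visit schedule in Section 7.1 is not split by arm, and Section 4.3 has each dietician cover all five groups.

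**Step 4. Which stated outcomes depend on this?** None of the main or secondary outcomes in Sections 8.2.2 and 8.2.3 is an AE count. The safety sub-study in Section 7.6.3 rests mainly on named serum and urine measures.

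**The case against.** The best defence turns on the word "also". The sentences before it concern the registration of treatment, so it most naturally means in addition to that registration. A reader might infer that Section 7.8.1 itself orders a second AE on top of the condition treated. It does not, since it never mentions the condition. A sensible investigator could take the rule as a prompt to look for the cause and file one AE report for it. This stands in part: double recording is a possible result of reading two sections together, not an explicit instruction. It does not remove the conflict, because the sentence still makes the medication change the AE and nothing limits it to changes caused by a new or worsened condition.

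A reader might also infer that the safety comparison between diets is biased. The protocol does not support that: it describes no comparison of AE counts between arms and gives no sign that prescribing would differ by diet. Counting and de-duplication rules are commonly left to an SAP in any case.

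Third, over-reporting is the cautious direction, and the medication record may allow later reclassification. That is fair, and it keeps the point small. But Section 7.8.1 does not ask for the indication or for a link to the event treated, so clean reclassification is not assured.

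Finally, reporting to the Ethical Officer need not lead to action, since Section 9.3 ties action to AEs of clinical significance. Section 7.6.3 speaks of adverse effects rather than AEs, so the reporting route rests on Section 9.3 alone.

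**Conclusion.** The point holds as a contradiction between two adjacent sections, and it is minor. It follows from the text without any numerical assumption: as written, Section 7.8.1 labels as AEs some things that Section 7.8 does not count as AEs.

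The direction of the effect on AE records and event counts is upward. Its size is unknown, and the worked range only restates assumed values of f. No percentage inflation should be quoted as a property of this trial. The practical harm is an AE record, and a stream of reports to the Ethical Officer, that contains some non-events and possibly duplicates. The weight and body composition results do not depend on it.

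**What to change.** Replace the last sentence of Section 7.8.1 with text to this effect: new medications and dose increases are recorded as concomitant treatment together with their indication; the indication is reported once as an AE if it meets the definition in Section 7.8; the change of medication is not itself an AE.

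This keeps the useful part of the rule, since a medication change still prompts the question of whether something untoward lies behind it. The cost is one sentence and, if the concomitant medication form lacks it, a field for the indication. No information is lost, because concomitant medication is already registered at the visits. If recruitment has begun, records already filed under the old sentence should be checked once against their indication.

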### **7.8.2 PREGNANCY**

Subjects who become pregnant during the study will be excluded (but the rest of the family will be allowed to continue).

## **7.9 STUDY MATERIAL & QUESTIONNAIRES (ADULTS ONLY)**

### **7.9.1 LCD DIET**

The diet used for the 8-week LCD weight loss period will be purchased from a manufacturer of LCD diets. The items used will include powder diets and/or snack bars.

### **7.9.2 DIETARY INTERVENTION PERIOD 1**

All dietary items will, if possible, be sponsored by local food manufacturers.

### **7.9.3 SCREENING QUESTIONNAIRE**

This includes questions relating to previous dieting experience, health, education, weight and lifestyle habits.

### **7.9.4 EATING DISORDER QUESTIONNAIRE**

This will be used during screening to identify subject eating disorders.

### **7.9.5 FUNCTIONAL QUESTIONNAIRE**

This will be used on CID 1-3 to measure possible changes in mental performance (cognitive functioning) during and after weight loss.

### **7.9.6 ATTITUDINAL/PSYCHOSOCIAL QUESTIONNAIRE**

This will be used on CID 1-3. It includes questions relating to behavioural and psychosocial factors (self efficacy, family coherence, motivation, etc), behaviour related to weight control, a Quality of Life questionnaire and the Stunkard 3-factor eating questionnaire (restraint, disinhibition and hunger).

### **7.9.7 FOOD CHOICE QUESTIONNAIRE**

This will be used on CID 1-3 to measure changes in food choices or preferences relating to the degree of satiety, whether sweet or savoury etc. It will be administered to 65 subjects at each centre during the OGTT (before and 30 min after the glucose load) and to 30 subjects (subgroup a) during

the meal test (before and 30 min after the meal). The questionnaire has 2 components: a Forced Choice Photographic Questionnaire and a Food Preference Checklist.

#### **7.9.8 HEDONICS/HUNGER QUESTIONNAIRE**

This scheme is part of the food diaries and will ask questions about social factors related to eating.

#### **7.9.9 END OF DAY QUESTIONNAIRE**

This will be used on CID 1-3 and weighing days approximately every other week. It will be completed in the subject's own home (on their own computer) at the end of the day and will ask questions relating to hunger, motivation, mood and subjective sensations/experiences.

#### **7.9.10 BALANCED INVENTORY OF DESIRABLE RESPONDING (BIDR) QUESTIONNAIRE**

It measures an individual's tendency to give socially desirable responses.

#### **7.9.11 VAS SCHEMES**

Subjective appetite ratings (hunger, satiety, fullness, prospective food consumption etc) are measured using computerised VAS scores (100mm scale). The scales will be completed on CID 1-3 during the OGTT and meal test (Subgroup a) at specific time points.

## **8. DATA MANAGEMENT**

### **8.1 DATA QUALITY ASSURANCE**

All study data will be entered as source documents. Data recorded in these documents will be collected in accordance with good clinical practice (GCP). All data management will be carried out in accordance with the protocol, GCP and ICH guidelines.

A central Data Hub (RTD6, coordinated by [name], Copenhagen University Hospitals, Danish Epidemiology Science Centre, Copenhagen, Denmark) will facilitate the integration between RTD lines, by standardization of protocols and data collation, storage of (and access to) RTD line data, rapid and detailed analysis of complex data sets.

### **8.2 STATISTICAL PROCEDURES**

All statistical analysis described in this protocol will be performed by the investigator. All analysis and tabulations will be performed using the latest release of the SAS® or SPSS software or similar statistical software. Appropriate descriptive statistics will be presented for each variable; n=number of patients, mean, median, SD and min-max for continuously distributed variables, and rates and percentages for categorical variables. Statistical tests will be performed using 5% as the nominal level of significance and interval estimates will be constructed using 95% as the level of confidence. Statistical and analytical methods, and sample size considerations are discussed in the following sections. The investigator will make the decisions regarding subjects, or individual values belonging to a patient, to be excluded from the analysis. Subjects will only be excluded from the efficacy analysis when the uses of these are considered a protocol violation, putting the scientific aspects of the trial at risk. The variables that will be statistically tested are given in the Sections concerning primary and secondary variables.

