### 4.3 BLINDING

Due to the characteristics of the study design where the dietetic guidance of the study subjects is the inherent intervention in the study, any blinding of the dietician or subjects is not possible. Each dietician will be responsible for guidance of subjects in all five dietary intervention groups.

By any analyses of data obtained prior to study termination, it will be assured that these analyses will not influence the ongoing study and hence the final outcome of the study.

These restrictions will be inferred to exclude any bias introduced by the study personnel.

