#### Handling of missing values

Since the sample size estimations take into account the drop-outs during the study, sufficient data should be obtained.

The primary analysis of data will be an "intention to treat" analysis (with only actual values presented) and will include only subjects having completed the study. We will also perform sensitivity analyses by examining different models of missing data and describe the range of possible outcomes based on the various models. For example, we will perform a "baseline carried forward" analysis and a "last observation carried forward" analysis as part of the sensitivity analysis.

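### Investigator-discretion exclusions and removal of severe protocol violators contradict the intention-to-treat label and can bias the open-label diet comparison

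*Protocol*

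**What the plan says.** Four parts of the protocol bear on who is counted.

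- **Section 8.2** assigns the analysis: "All statistical analysis described in this protocol will be performed by the investigator". It then assigns the exclusions: "The investigator will make the decisions regarding subjects, or individual values belonging to a patient, to be excluded from the analysis". The next sentence sets a limit for whole subjects: "Subjects will only be excluded from the efficacy analysis when the uses of these are considered a protocol violation", with the added condition that the violation endangers the trial scientifically. No violations are listed, and the limit does not mention individual values.
- **Section 5.3** says "Subjects may also be withdrawn from the study because of severe protocol violations", and then "These subjects will not be included in the analysis and will permanently be dismissed from the study". Reasons for dismissal are to be recorded in the source data. The protocol does not define a severe violation.
- **Section 8.2.4, Handling of missing values**, says "The primary analysis of data will be an 'intention to treat' analysis", and in the same sentence that it "will include only subjects having completed the study".
- **Section 4.3** says that "any blinding of the dietician or subjects is not possible". It describes no masking of the investigator, the analyst or the data review.

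**The concern.** An intention-to-treat comparison keeps each randomised subject in the allocated group whatever happens afterwards. Sections 8.2 and 5.3 let conduct after randomisation decide who is counted, and section 8.2 gives that decision to the person who also runs the analysis. Nothing requires the decision to be made without sight of diet group or outcome, or before the database is locked.

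The arms do not offer equal scope for a violation. Section 3 (dietary intervention period 1) stresses adherence in all five groups, but only groups 1 to 4 have a prescribed composition to depart from. Controls continue their usual diet and get no advice on composition. Detection is also unequal in period 1: the shop database in section 7.7.3 records food for everyone except controls. If departures from the diet go with weight regain, which is plausible but not stated, exclusions could fall unevenly on subjects with poorer outcomes. The primary comparison would then drift from the effect of being assigned a diet towards the effect in those judged compliant.

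Section 8.2.2 also makes drop-out rate a main outcome, and section 8.2.5 tests time to withdrawal. Read literally, section 5.3 could remove forced withdrawals from those analyses too.

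**Working it through.** The protocol gives no figure for exclusions, so there is none to reproduce. The check has two parts.

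**1. The rules side by side**

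- *Label:* intention to treat (8.2.4).
- *Set actually analysed:* completers (8.2.4), minus subjects dismissed for severe violations (5.3), minus subjects or values the investigator excludes (8.2).
- *Thresholds:* 'severe' in 5.3, and endangering the trial scientifically in 8.2. The two differ, and neither is defined.
- *Criterion for single values:* none.
- *Possible offsets:* the safeguard on data analyses in 4.3 covers those made before study termination, not exclusions. The baseline- and last-observation-carried-forward analyses in 8.2.4 deal with missing data, and nothing says that they restore excluded violators or values.

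The completers-only clause already removes dismissed subjects, because they cannot complete. What 8.2 adds is discretion over completers and over single values. The rules are still separate: if only the completers clause were repaired, 5.3 and 8.2 would go on removing randomised subjects.

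**2. How large an effect is possible (illustration only)**

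If a fraction p is excluded from one arm only, and the excluded average d kg more regain than those retained, the arm mean falls by p × d. With assumed values p = 0.05 and d = 2 kg this is 0.05 × 2 = 0.10 kg. If exclusion is unrelated to outcome, d = 0 and there is no shift.

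The ceiling is reached when the excluded are exactly the worst regainers. For a normal outcome:

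shift = SD × φ(z₁₋ₚ) / (1 − p)

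Inputs: SD 2.01 and 2.5 kg (both in section 8.2.7), and 100 and 125 subjects per group. Section 8.2.7 states 125; 100 is what an exact t-test needs for 1.0 kg, SD 2.5 kg and 80% power. The values of p are assumptions. Type I error comes from 20,000 simulated two-sided 5% t-tests per setting, with no true diet effect and subjects treated as independent.

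| p, one arm only | φ/(1 − p) | Shift, SD 2.01 | Shift, SD 2.5 | Type I error |
|---|---|---|---|---|
| 2% | 0.0484/0.98 = 0.0494 | 0.10 kg | 0.12 kg | about 7% |
| 5% | 0.1031/0.95 = 0.1086 | 0.22 kg | 0.27 kg | about 13–15% |
| 10% | 0.1755/0.90 = 0.1950 | 0.39 kg | 0.49 kg | about 30–34% |

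Against the planned 1.0 kg, the illustrated range runs from nothing to about half the planned effect.

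**The case against.** Subject exclusion is not unlimited. Section 8.2 confines it to violations that endanger the trial scientifically, and section 5.3 says that subjects may be withdrawn, only for severe violations, with reasons recorded. A separate analysis plan could define both terms. This narrows the point, since not every violator is dropped. It does not remove it: the limit is still a judgement by the person running the analysis, it does not reach single values, and an analysis plan that kept everyone would contradict the protocol.

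A reader might infer three stronger things that the text does not support.

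- *That the investigator is unblinded and decides with outcomes in view.* Section 4.3 names only dieticians and subjects, and no passage says when exclusions are decided. The protocol provides no masking, but that is silence.
- *That non-adherence is the violation meant.* Section 5.3 treats refusal to follow dietary instruction in a separate paragraph, and does not call it a severe violation.
- *That the rule must bias the result, always in favour of the harder diet.* Exclusion unrelated to outcome causes no shift.

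Section 4.3 also says that its restrictions are taken to exclude bias from study personnel. Those restrictions are that each dietician serves all five groups and that data analyses before termination must not influence the ongoing study. Neither governs exclusions.

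**Conclusion.** The point holds as a defect in rules that the protocol itself states. Sections 8.2 and 5.3 permit randomised subjects, and single values, to be removed without predefined criteria or masked review. That contradicts the intention-to-treat label, as does the completers-only clause beside it.

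The consequence is that the comparison *can* be biased; the documents do not show that it will be. Neither direction nor size can be derived from them. The 0.22 to 0.27 kg at 5% and 0.39 to 0.49 kg at 10% assume exclusion in one arm only and removal of exactly the worst regainers. They are ceilings for those assumed rates, not estimates. The case for change rests on the contradiction and the lack of safeguards, not on these kilograms.

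**What to change.** Change three places together, because changing any one alone leaves the others in conflict with it.

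- **Section 8.2:** replace the discretion sentence and the limit that follows it. The primary analysis includes all randomised subjects as allocated, with all valid recorded values. A value is excluded only for documented data error under criteria fixed in advance, decided and listed by someone masked to diet group before database lock.
- **Section 5.3:** replace the sentence that leaves dismissed subjects out of the analysis. Week 26 and week 52 weights are sought whatever the subject's adherence or withdrawal status, subject to consent. This concerns data collection and analysis only and adds no rule on stopping the diet.
- **Section 8.2.4:** reconcile the completers-only clause with the intention-to-treat label, and name how missing weights are handled in the primary analysis.

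Violators are left out only in a supportive per-protocol analysis, with qualifying violations listed in advance.

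The cost is wording changes, some extra follow-up weights and one masked listing review. The central Data Hub in section 8.1 stores and collates the data, but the protocol gives it no masking role, so that task would have to be assigned.
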